## **7. OBJECTIVES**

### **7a. Primary objective and hypothesis**

Post-exertional malaise (PEM) symptoms of post-COVID-19 subjects and age/sex matched controls in response to three different exercise trials. The primary outcome is the comparison of the change in fatigue rating using the visual analog scale (VAS) 0-10 before and 48h after each training trial between the post-COVID-19 group and the control group. We hypothesize that the post-COVID-19 group will suffer from persistent fatigue at 48h after exercise compared to baseline, whereas control group will return to the baseline level at this time point.

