## **9. METHODS: PARTICIPANTS, INTERVENTIONS AND OUTCOMES**

Thirty post-COVID-19 patients will be recruited through the post-COVID-19 clinic at Karolinska University Hospital Huddinge or other channels (advertisements posted on the Karolinska Institute website, social channels, information boards, and advertisements on the Swedish Post-COVID-19 patients' organization webpage and social channels. Interested participants contacted us for further information. Interested participants contacted us for further information Patients should be aged between 18–64 years, experienced persisting symptoms at least 3 months, including post-exertional exacerbation symptoms, and had no previous history of cardiovascular disease, general anxiety syndrome or somatic symptom disorder. In addition, 30 healthy control subjects, matched for sex, age and physical fitness will be also recruited from the community (advertisements posted on the Karolinska Institute website, social channels and information boards). All subjects will perform a comprehensive set of physiological assessments, including COVID-19-related symptoms, post-exertional symptoms, neurophysiological function, cardiovascular and circulatory function, respiratory/ventilatory function, maximal oxygen uptake, muscle strength, physical function, blood status, and cytokine profiling. Subjects will then complete 3 exercise trials in a randomized counterbalanced order: continuous moderate-intensity training (MICT), high-intensity interval training (HIIT), and strength training (ST). The acute exercise response will be thoroughly and continuously monitored, including measurements of O2 saturation, blood pressure, ventilatory response, oxygen uptake, and blood lactate. In addition, blood samples will be collected before, immediately after, and 1 hour after each exercise session to describe leukocyte and cytokine release. After a 48-hour rest period following each exercise session, patients will return to the laboratory for symptom assessment, graded exercise testing, and blood sampling. Finally, after 1 year, we will perform a physiological follow-up using the same measurements as the baseline examination. Figure 1 shows the study design divided into two main parts, physiological assessment (A; comprehensive physiological characterization and 1 year follow-up, B; acute exercise sessions).

[figure not shown]

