### **14. SAMPLE SIZE**

Determining an appropriate sample size for this study was challenging as the post-COVID-19 syndrome was new and there was no established data on the expected effect size of the interventions and the consistency of patient responses. Nevertheless, based on clinical observations from previous studies, we expected a markedly different response to exercise in patients compared to controls. Indeed, symptom variability after acute exercise in myalgic encephalomyelitis/chronic fatigue syndrome (ME/CFS) shows moderate to large effect sizes for most symptoms assessed with VAS scales. Our a priori estimate (using G\*Power) was that we would need at least 28 patients and 28 controls to detect a moderate effect size (Critical F 0.25) between groups in a within-between interaction design with a power of 80% and an alpha of 5%.

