### **16. ALLOCATION**

The research team will randomly allocate the order of exercise interventions. Same allocation will be applied in both groups. Research Electronic Data Capture (Redcap) software will be used for the random allocation. In addition, exercise order will be recorded and incorporated into the statistical model.

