## **20. STATISTICAL METHODS**

Analyses will be performed using IBM SPSS Statistics for Windows, version 29.0 (Armonk, NY: IBM Corp). To assess the primary outcome (post-exertional symptom exacerbation from baseline to 48h after each exercise), a mix-linear model was initially planned to analyse the differences in symptom changes following three exercise sessions (HIIT, MICT, ST), between the two groups (post-COVID-19 patients vs. control). Subject ID and the order of exercise sessions will be used as random effect in the mix-linear model. Pairwise comparisons will be performed when significant main or interaction effects are detected, using Bonferroni correction.

However, during data analysis, the aforementioned statistical plan was amended given the nature of the data (not normally distributed data). Particularly, a significant number of the control subjects responded “zero” change in the visual analog scale assessing the symptom exacerbation. As such, non-parametric tests (Mann-Whitney test, Kruskal-Wallis test) were used to compare differences in symptoms following exercise trials between the groups.

A mixed-linear model was used to analyze differences in continuous data (CPET variables, interleukin (IL)-6, Creatine Kinase) following three exercise sessions (HIIT, MICT, ST) between the two groups (post-COVID-19 patients vs. control). Subject ID and order of exercise sessions were used as random effect in the mix-linear model. Pairwise comparisons will be performed when significant main or interaction effects are detected, using Bonferroni correction.

For the physiological characterization assessments, two-tailed Chi-square test or Student t-test will be used to examine differences in categorical or continuous variables, respectively, between the post-COVID-19 patients and the control group.

Results will be presented as mean (SD), and significance will be set at  $P < 0.05$ .

Missing data will be treated as missing values in the statistical models, unless otherwise specified. In retrospect, there was no need for missing data imputation. Therefore, missing data were treated as missing values.

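### The amended primary analysis names Mann-Whitney and Kruskal-Wallis tests without saying what each one compares; group by session and order drop out, no multiplicity rule covers the sessions, and Kruskal-Wallis would ignore the pairing if used across them

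*Combined protocol and SAP*

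**What the plan says.** Section 9 gives a within-person design: "Subjects will then complete 3 exercise trials in a randomized counterbalanced order". Section 7a defines the primary outcome as the change in fatigue on a 0–10 visual analogue scale, "before and 48h after each training trial between the post-COVID-19 group and the control group". Each person therefore supplies three 48-hour change scores.

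Section 20 first describes a mixed model for this outcome: "Subject ID and the order of exercise sessions will be used as random effect in the mix-linear model". It then reports that during data analysis, because the changes were not normally distributed and many controls reported zero change, "non-parametric tests (Mann-Whitney test, Kruskal-Wallis test) were used to compare differences in symptoms following exercise trials between the groups". The mixed model with subject and order is kept for the CPET variables, IL-6 and creatine kinase. Section 25 dates the change to August 2023.

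Two other current statements bear on this. Section 16 says that "exercise order will be recorded and incorporated into the statistical model", and also "Same allocation will be applied in both groups". Section 14 sizes the trial as needing "at least 28 patients and 28 controls to detect a moderate effect size (Critical F 0.25) between groups in a within-between interaction design".

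**The concern.** Mann-Whitney and Kruskal-Wallis are tests for independent samples. Non-normality and many zeros are a reason to leave a normal-theory model. They are not a reason to give up the pairing of sessions within a person, because rank and ordinal methods exist that keep it.

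The amended text does not say whether the tests were run per session, across sessions, or on all sessions together, and these uses behave very differently. The Bonferroni rule in Section 20 is attached to pairwise comparisons after a significant main or interaction effect in the mixed model. The rank tests produce no such effects, so no multiplicity rule is stated for three per-session comparisons.

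At stake are the error rate of the patient–control claim and the power of the comparison between exercise types. The latter matters because session order is the only thing randomised. The change was made after data analysis had begun, so an exact specification matters more than usual.

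**Working it through.** **Inputs.** From the documents: three sessions per person; two groups; alpha 5%; 28 per group in Section 14, 30 in Section 9 and 40 in the synopsis. Not in the documents, so assumed: within-person correlation of the change scores, ρ = 0.3, 0.5 and 0.7; SD of change 2 points. Simulations used rounded change scores, including settings with about 55% zeros, and roughly 1,000 to 4,000 runs per cell.

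**1. The plan's own figure.** For a within-between interaction with two groups and m measurements, λ = f²·N·m/(1−ρ), with m−1 and (N−2)(m−1) degrees of freedom. Section 14 gives f = 0.25 and 28 + 28, but neither m nor ρ.
- m = 3, ρ = 0, N = 56: λ = 0.0625 × 56 × 3 = 10.5, power 82%.
- m = 3, ρ = 0.5, N = 28 in total: λ = 0.0625 × 28 × 3 / 0.5 = 10.5, power 81%. With N = 56, λ = 21 and power is 99%.

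The figure cannot be settled without m and ρ, and that is a separate matter. What counts here is that the sizing target was a group-by-within interaction, which neither named test can examine.

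**2. Mann-Whitney, one test per session.** Each test uses one value per person from two separate groups, so its independence assumption holds across people. Simulated size is 4.6% to 5.3% at 28 and 30 per group, and 3.5% to 5.5% at 40 with fewer runs. With a period effect of 0, 0.5 and 1 point and identical balanced orders in both groups, size is 4.5%.

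Familywise error over three uncorrected tests, if independent: 1 − 0.95³ = 14.3%. With correlated sessions the simulations give about 11% to 15%. With Bonferroni the independent-case bound is 1 − (1 − 0.05/3)³ = 4.9%, and the simulated values are at or below 5%.

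**3. Kruskal-Wallis across the three sessions within a group.** The test expects between-session variation of the size seen between different people. Within-person correlation shrinks that variation by about (1−ρ), so approximate true size = P(χ²₂ > 5.991/(1−ρ)) = exp[−5.991/(2(1−ρ))].
- ρ = 0.3: exp(−4.28) = 1.4%
- ρ = 0.5: exp(−5.99) = 0.25%
- ρ = 0.7: exp(−9.99) = 0.005%

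Simulation gives about 1.4% to 1.7%, 0.4% to 0.9%, and 0.1% or less. Friedman holds 4.2% to 5.0%.

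Power for a 1-point shift in one session, n = 30, as ranges over simulation settings:

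| ρ | Kruskal-Wallis | Friedman |
|---|---|---|
| 0.3 | 41–45% | 53–54% |
| 0.5 | 36–41% | 65–69% |
| 0.7 | 34–37% | 84–89% |

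Run over all six group-by-session cells, Kruskal-Wallis is also conservative (size about 2.7% to 4.1%).

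**4. Mann-Whitney on all sessions pooled.** The variance of the comparison is understated by 1 + 2ρ, so approximate true size = 2[1 − Φ(1.96/√(1+2ρ))].
- ρ = 0.3: 1.96/1.265 = 1.55, size 12%
- ρ = 0.5: 1.96/1.414 = 1.39, size 17%
- ρ = 0.7: 1.96/1.549 = 1.27, size 21%

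Simulation gives about 10% to 20%.

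**5. Order.** Section 16 commits to having order in the model. The tests in Section 20 for the primary outcome cannot include it. The two sections disagree as they stand.

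**The case against.** The strongest reply is that the primary contrast is between groups after each session. Sections 7a and 20 read most plainly as one Mann-Whitney test per session, and that test is valid. A reader might infer that the primary P values are wrong because repeated sessions were treated as independent. The documents do not support that. They state neither pooling nor a Kruskal-Wallis test across sessions. The latter is an inference from there being only two groups, for which Kruskal-Wallis is not needed.

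The two problem uses also err in opposite directions. Kruskal-Wallis across sessions makes false positives rarer, so a significant result from it would not be spurious. Nor is a finding of no difference between exercise types guaranteed by construction: at ρ = 0.3 the power gap is about 42% against 53%, and it becomes large only at higher assumed correlations.

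Omitting order shows no bias in the group contrast if both groups follow the same balanced orders, as Section 16 indicates. Subject and order also remain in the models for CPET, IL-6 and creatine kinase. Departing from the superseded mixed model is not in itself an error.

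All of this stands, and it limits the point. It does not remove it. The valid reading is not written down, that reading has no multiplicity rule, the interaction is untested, and Section 16 still promises something the primary analysis does not do.

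**Conclusion.** The concern holds as one of incomplete specification and lost design information. It does not show that the primary P values are invalid.

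The patient–control contrast is sound if tested once per session, but without a stated correction the familywise error is about 11% to 15%. If Kruskal-Wallis was used across sessions, it ran at about 0.1% to 1.7% instead of 5%. It would then have had about 34% to 45% power where Friedman has 53% to 89%, so a null result on exercise type would be weak evidence. If sessions were pooled, type I error was about 10% to 20%.

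The sizes rest on assumed values (correlation 0.3 to 0.7, SD 2, a 1-point shift). The direction of each effect requires only positive within-person correlation. The statement that omitting order is harmless to the group contrast rests on the order allocation being the same in both groups.

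**What to change.** For the primary outcome, specify a rank-based or ordinal repeated-measures model with group, session, group × session and period as fixed effects and subject as a random effect. This copes with the zeros, keeps the pairing, restores the interaction and meets the Section 16 commitment on order.

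If simple tests are kept:
- State the unit of each test.
- Use one Mann-Whitney test per session for the group contrast, with Bonferroni or Holm over the three sessions.
- Use Friedman within group for comparisons between sessions.
- Never pool sessions as independent observations.

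In either case, report effect estimates with 95% confidence intervals. Because the change was made during data analysis, also give the originally planned mixed model as a sensitivity analysis. Reconcile Section 16 with Section 20 on order; if simple tests are kept, say that order is not modelled for the primary outcome.

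The cost is revised SAP wording and a small amount of extra analysis on data already held.

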Physiological (comprehensive) characterization post-COVID-19 subjects and comparison with age/sex matched controls will provide knowledge on the physiological phenotype of the post-COVID-19 group. Numerous clinical examinations will be used to assess the physiological function of post-COVID-19 patients and compared to age/sex matched controls. Specifically, echocardiography and arteriography will be used to assess cardiovascular function, spirometry to assess respiratory function, cardiopulmonary exercise testing and 6-min walk test to assess exercise capacity, handgrip and isokinetic dynamometer to assess the muscular strength of upper and lower body respectively, CO-rebreathing method to assess blood and plasma volume, and head up tilt-test to assess dysautonomia. In addition, neurophysiological assessment includes nerve conduction studies, sympathetic skin response, heart rate variability studies, and needle EMG. Questionnaires, blood samples and muscle biopsy will be also collected and compared between the groups.

Finally, physiological function at 1y follow-up in post-COVID-19 patients and age/sex matched controls will be assessed. Same clinical investigations as the

baseline assessment will be performed at 1y follow-up in post-COVID-19 patients and age/sex matched controls. Comparisons within and between groups from baseline and 1y follow-up will be performed.

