## **8. TRIAL DESIGN**

This is a prospective interventional randomized two-arm crossover designed study. Two experimental groups: a) post-COVID-19 syndrome patients and b) age- and sex-matched healthy controls performed 3 different exercise sessions in a randomized counterbalanced order. Researchers will be blinded during the data analysis and during the data collection as far as possible.

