Germany). The test will be considered maximal ( $\text{VO}_{2\text{peak}}$ ) when two or more of the following criteria are reached: 90% of age-predicted HR ( $220 - \text{age}$ ), a respiratory exchange ratio (RER)  $\geq 1.1$ , a peak  $\text{bLa}$  of  $\geq 6 \text{ mmol}\cdot\text{l}^{-1}$ , or a perceived exertion  $\geq 18$ .  $\text{VO}_{2\text{peak}}$  will be determined as the highest 20-second average. Subjects will be verbally encouraged during the test to increase their motivation for maximal exertion.

**Arteriography:** Measurements of aortic pulse wave velocity ( $\text{PWV}_{\text{ao}}$ ) will be performed using non-invasive technique (Arteriograph, TensioMed Ltd., Budapest, Hungary). Participants will be rested in supine position for at least 10 minutes, and then a single upper arm cuff will be placed to measure  $\text{PWV}_{\text{ao}}$ . The device first measures the brachial blood pressure and then inflates the cuff to suprasystolic pressure to occlude the brachial artery. During this period, the cuff collects pure pressure signals and detects direct and reflected systolic wave peaks. The time difference between the early and late systolic peaks is equal to the time of the aortic pulse wave traveling down to the aortic bifurcation and back towards the heart. The aortic root-bifurcation transit time can be calculated, and by estimate the straight distance between the suprasternal notch and pubic bone (an acceptable estimate of the aortic length), the  $\text{PWV}_{\text{ao}}$  will be calculated by the software.

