**Blood volume:** The optimized carbon monoxide rebreathing method will be used to determine tHb, from which BV and PV later were calculated using hemoglobin concentration [Hb] and hematocrit (Hct). Subjects will rest for 15 minutes before a venous blood sample will be taken from the median cubital vein. The sample will be immediately analyzed for baseline carboxyhemoglobin (%HbCO), [Hb] and Hct. End-tidal carbon monoxide (CO) will be measured at baseline and after rebreathing using a CO gas analyzer (Dräger, PAC 700, Lübeck, Germany and Honeywell, BW Solo, Charlotte, NC, USA). Throughout rebreathing, the same gas analyzer will be used to check for CO leaks. Subjects will breathe a gas mixture of chemically pure (99.97%) CO ( $0.8 \text{ mL} \times \text{kg}^{-1}$ ) and medical oxygen (AGA, Stockholm, Sweden) for 2 minutes before disconnecting from the spirometer (Blood tec GmbH, Bayreuth, Germany). Two venous blood samples (1 mL) will be taken, one before rebreathing and one 7 minutes after administration of CO. The samples will be then analyzed in duplicate for %HbCO (ABL 90 Flex, Radiometer A/S, Copenhagen, Denmark), tHb will be calculated as previously described.

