## **18. DATA COLLECTION**

At baseline and at 1-year follow-up, all physiological variables will be assessed under strictly standardized procedures in a laboratory setting. Physiological functions of the patients with post-COVID-19 condition will be compared with a well-matched healthy control group in an exploratory manner, as this patient population has yet to be characterized. Measurements before and after 1 year will be compared to determine if improvements are more related to certain physiological factors than others. Figure 1 and section 12 provide details in regards to the data collection for each particular outcome.

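### Pulse wave velocity and blood volume are compared between non-randomised groups by unadjusted t-test only, although blood pressure and body mass are at hand and could account for a difference

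*Combined protocol and SAP*

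**What the plan says.** Section 20 (Statistical methods) gives one rule for the whole characterisation battery: a "two-tailed Chi-square test or Student t-test will be used to examine differences in categorical or continuous variables, respectively", at P < 0.05. It names no covariate, no scaling and no use of the matching.

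Section 7b places arteriography and CO-rebreathing blood and plasma volume in that battery and says that the comparison "will provide knowledge on the physiological phenotype of the post-COVID-19 group". Section 18 adds that physiological functions "will be compared with a well-matched healthy control group in an exploratory manner".

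On matching, the synopsis and Section 8 name age and sex ("age- and sex-matched healthy controls performed 3 different exercise sessions"). Section 9 has controls "matched for sex, age and physical fitness will be also recruited from the community", without saying how fitness is measured or how close the match must be. No section names blood pressure or body mass as a matching factor. Section 16 randomises only the order of the exercise sessions.

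Both covariates are nevertheless available. Under Arteriography in Section 12, "The device first measures the brachial blood pressure and then inflates the cuff to suprasystolic pressure". Under Blood volume, total haemoglobin is determined, "from which BV and PV later were calculated using hemoglobin concentration" and haematocrit, and the CO amount is 0.8 mL per kg, so body mass must be known. The text does not say whether the volumes are analysed in litres or per kg.

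**The concern.** PWVao depends on the pressure at which it is measured, and absolute blood volume scales with body size. In a randomised comparison both would balance on average. Here group membership is a diagnosis, so nothing balances them apart from whatever the matching on age, sex and possibly fitness brings along. If patients and controls differ in pressure or mass, the difference passes into the t-test. The reader then cannot tell whether the arteries differ at a given pressure, or the volume at a given body mass.

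This bears on the stated use of the results. Section 7b wants a physiological phenotype, and Section 6b hopes the findings will help decide which tests to perform in the clinic. There is also a plainer cost. With perfectly balanced groups, a strong predictor left out of the model stays in the error term and widens the interval.

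**Working it through.** **The plan's own figures.** There is none to reproduce for these measures. Section 14 (28 + 28, effect size 0.25, 80% power, 5% alpha) covers a within-between interaction design and does not extend to PWVao or blood volume. The documents give no SD, correlation or expected imbalance for PWVao, volume, pressure or mass.

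**Inputs**
- Group size: 30 per group (Section 9) or 40 per group (synopsis). The documents give both, so both are used.
- Test: two-sided two-sample t-test at 5% (Section 20).
- Assumed: within-group correlation r of 0.4–0.6 between outcome and covariate.
- Assumed: imbalance d in the covariate of 0.3–0.5 SD.
- Assumed: one covariate; age and sex are left out of the illustration.

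**Step 1: difference carried by the covariate.** With no direct group effect, the expected difference in the outcome is r × d in outcome SDs.
- Low end: 0.4 × 0.3 = 0.12 SD.
- High end: 0.6 × 0.5 = 0.30 SD.

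**Step 2: how often the unadjusted test rejects.** The noncentrality is r × d × √(n/2), with 2n − 2 degrees of freedom.

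| n per group | r × d | Noncentrality | Rejection |
|---|---|---|---|
| 30 | 0.12 | 0.12 × √15 = 0.465 | 7.4% |
| 30 | 0.30 | 0.30 × √15 = 1.162 | 20.8% |
| 40 | 0.12 | 0.12 × √20 = 0.537 | 8.3% |
| 40 | 0.30 | 0.30 × √20 = 1.342 | 26.3% |

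With d = 0 the rate is 5.0% whatever r is.

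**Step 3: check of the adjusted model.** Simulation with 4,000 runs per scenario, 30 per group and no direct group effect:

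| d | r | Unadjusted | Adjusted |
|---|---|---|---|
| 0.3 | 0.5 | 8.9% | 5.3% |
| 0.5 | 0.7 | 26.0% | 4.6% |
| 0.8 | 0.8 | 67.5% | 5.0% |

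The last two scenarios lie outside the range used above. They only show that adjustment still returns the rate to about 5%.

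**Step 4: precision with no imbalance.** The range r = 0.4–0.6 corresponds to R² = 0.16–0.36. Adjustment shrinks the residual SD by √(1 − R²), so a 0.5-SD difference behaves like 0.5/√(1 − R²):
- R² = 0.16: 0.5/√0.84 = 0.546.
- R² = 0.36: 0.5/√0.64 = 0.625.

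| n per group | Unadjusted power | R² = 0.16 | R² = 0.36 |
|---|---|---|---|
| 30 | 47.8% | 54.7% | 66.3% |
| 40 | 59.8% | 67.3% | 78.8% |

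The degree of freedom spent on the covariate changes these by less than 0.1 percentage point.

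**The case against.** The strongest reply is that the t-test validly answers the question it asks, namely whether the groups differ. Section 6a lists deconditioning, orthostatic intolerance and dysautonomia as candidate mechanisms of exercise intolerance. If the condition changes pressure or body mass, those variables lie on the disease pathway, and adjusting for them removes part of the phenotype that Section 7b sets out to describe. This stands. It is why the adjusted estimate belongs beside the unadjusted one and cannot replace it. It is also why the rates in Step 2 should not be called false-positive rates: a real marginal difference in PWVao is not an error for the t-test.

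A reader might infer that the plan will label any group difference as arterial stiffening or abnormal volume. The documents do not say so. Section 18 calls the comparison exploratory, Section 7b speaks of a phenotype, and no cut-off or rule for an abnormal PWVao or volume is given. What stands is that the planned analysis leaves the two explanations unseparated.

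A reader might also take it that volume is confounded by body size. That holds only if volume is analysed unindexed, and the unit is not stated. A per-kg value would already remove much of the size effect. The PWVao part does not depend on this.

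Fitness matching in Section 9 might limit an imbalance. It is undefined, is absent from the synopsis and Section 8, and is not a match on pressure or mass, so it weakens the concern without removing it.

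Finally, these are two measures in a large exploratory battery, and the values are recorded, so the analysis could be added at any time. That argues for low priority. It does not argue for leaving the model unspecified.

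**Conclusion.** The point holds as a minor, inexpensive improvement. Section 20 plans only an unadjusted comparison of PWVao and blood and plasma volume between non-randomised groups, while two obvious covariates are available and unmatched. A difference in pressure, or in body size if volume is unindexed, could account for the result, and the plan has no means of showing whether it does. Even without imbalance, precision is given up.

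The percentages in the working illustrate that possibility and do not estimate what happened in this trial, because the correlations and imbalances are assumed throughout. The documents do not show that an imbalance exists, that differences would be reported as abnormalities, or that the adjusted estimate is the only right one. The outcomes are exploratory and secondary. The primary fatigue analysis and the sample size are unaffected.

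**What to change.** In Section 20, keep the unadjusted group difference and add, beside it:
- for PWVao, a linear regression on group, mean arterial pressure from the same arteriograph reading, age and sex;
- for blood volume and for plasma volume, a linear regression on group, body mass, age and sex.

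State in Section 12 or Section 20 whether the volumes are analysed in litres or per kg. Report both estimates with confidence intervals and say what each answers: the total difference between groups, and the difference at equal pressure or equal body mass. Say also that pressure and mass may themselves be affected by the condition. Section 25 records that the statistical plan was revised during data analysis in August 2023. If the characterisation data have been seen, label the added models as post hoc.

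The cost is a few lines of SAP text, one or two model terms per outcome beyond age and sex, and a second estimate for each outcome that has to be interpreted. No new data collection is needed.
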